#### Diagnostic committee review

In all cases, information gathered from the treating clinician's notes through the diagnostic proforma and the baseline clinical interview with the participant will be reviewed by the Diagnostic Committee for a final decision as to the diagnosis. The diagnostic committee comprises a panel of Sydney epilepsy specialists. Epilepsy will be defined according to the ILAE guidelines [64]. A clinical diagnosis will rely upon two criteria:

(a) Clear evidence of recurrent epileptic seizures, with evidence that these are unprovoked by any acute medical condition or transient brain disorder; and

(b) Documentation of diagnosis by someone with appropriate specialized training in the recognition of epilepsy. This allows for the inclusion of those who have an enduring predisposition to generate epileptic seizures yet have only had one seizure.

Each participant will be allocated to one of the following groups:

*Definite epilepsy*, with primary documentation that meets criteria: a) clear evidence of two or more unprovoked epileptic seizures that have occurred over interval(s) exceeding 24 hours, or b) confirmed diagnosis of epilepsy by a health care provider with appropriate specialised training in the recognition and treatment of epilepsy.

*Probable epilepsy*, with other sources of information indicating the likelihood that criteria (a) or (b) are met. Documentation of a diagnosis of epilepsy by a trained non-specialist health care provider without specific documentation of definite criteria above.

*Possible epilepsy*: requires further information from the baseline interview to confirm this and identify the seizure type classification.

*Other seizure type: *provoked seizure (acute symptomatic) e.g. post acute head injury, non-epileptic non-organic seizures (panic, psychogenic etc), non-epileptic organic seizures (syncope etc)

Not epilepsy

### Statistical considerations

#### Sample size assumption

In the most recent census [52] there were 510,000 people usually resident in the Eastern zone of the SSWAHS. SEISMIC can expect to recruit 254 people with epilepsy per year for a total of 508 over the two year recruitment period. With an estimated 5% refusal, we can expect 484 people to be recruited.

##### Adults

In a Tasmanian cross sectional survey approximately 30% of adults with epilepsy reported psychological morbidity, which is associated with increased disability (e.g. taking more sickness or disability days). In an American study having chronic epilepsy and depression was associated taking 4 more disability days per month than those without [65]. If we hypothesise that participants with psychiatric co-morbidity experience 5 disability days vs. 3 disability days per month for those without psychiatric co-morbidity and the standard deviation (SD) of these is 4 then we are looking for an effect size of 0.5. With 90% power, an alpha of 0.05 would require a sample of 191 (64 with psychiatric co-morbidity, 127 without) to detect this difference in disability days per month (total sample 143 at 80% power). With the incidence assumptions from above, two years of recruitment would be adequate to detect this in working age adults and evaluate employment consequences of epilepsy as well as providing some leeway for multivariate modelling and interactions.

##### Children

In the SSWAHS 39% of families speak a language other than English at home. If we hypothesis that this is associated with a greater economic household impact through e.g. increased likelihood of not making a basic household payment, then the sample size recruited in two years above is sufficient to detect a relative risk of 1.5 for this poorer socioeconomic outcome.

### Statistical Analysis

The incidence of epilepsy will be reported as definite cases of epilepsy over the population of the study area. Incidence will also be reported by age and syndromic groups. Data analysis will use multivariable one-level (SAS Proc Genmod) as well as mixed model approaches, which take variations within cluster (patients) and between clusters (e.g. hospitals) into account (SAS Proc Mixed). Mixed model approaches will be of use when cluster and individual level data are used to explain a possible outcome, for example, process of care by hospital along with individual level data on language spoken at home as risk factors for adherence to medication.

Multivariable regression will be used to examine the contributions of protective and risk factors on several clinical, psychosocial and economic outcomes. Hypothesised and known risk factors from the literature will be used in the initial regression models, together with factors with a p-value of less than 0.2 in univariate analyses which will be considered as potential confounders. Relative risks and their corresponding 95% confidence intervals will be presented for risk factors as they relate to the outcomes of interest.

Since the length of follow-up for participants will differ depending on the date of diagnosis and hence enrolment into the incident cohort, length of time in the study (and therefore at risk) will be taken into account in regression models. Potential effect modifiers will be examined by inserting interaction terms into the multivariable models.

Survival analyses will be used to investigate the time trajectory of risk and protective factors for various poor outcomes. Kaplan-Meier survival curves will be produced and then the adjusted survival will be examined using Cox proportional hazards models in order to take into account multiple exposure variables.

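### For binary outcomes, the procedure named for clustered analyses (SAS Proc Mixed) does not give the relative risks that the plan promises

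*Protocol article*

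**What the plan says.** The Statistical Analysis section of the protocol article fixes three things.

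- **Procedures.** "Data analysis will use multivariable one-level (SAS Proc Genmod) as well as mixed model approaches". The mixed models are those "which take variations within cluster (patients) and between clusters (e.g. hospitals) into account (SAS Proc Mixed").
- **Use of the mixed model.** It is meant for questions that combine cluster-level and individual-level data. The example is "process of care by hospital along with individual level data on language spoken at home as risk factors for adherence to medication".
- **Effect measure.** "Relative risks and their corresponding 95% confidence intervals will be presented for risk factors as they relate to the outcomes of interest".

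The same section adds survival methods, in which "the adjusted survival will be examined using Cox proportional hazards models in order to take into account multiple exposure variables".

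Two outcomes elsewhere show the range to be analysed. The Children section has a yes/no outcome, not making a basic household payment, and calls the sample "sufficient to detect a relative risk of 1.5 for this poorer socioeconomic outcome". The Adults section has a mean: the co-morbid group is assumed to "experience 5 disability days vs. 3 disability days per month for those without psychiatric co-morbidity and the standard deviation (SD) of these is 4".

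Table 1 schedules economic hardship at baseline, 4 months and 12 months. The section on case ascertainment and consent makes one year the primary endpoint.

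**The concern.** Proc Mixed fits a linear model with an identity link and normal errors. Applied to a yes/no outcome, its coefficient is a difference in risk. It also treats the residual variance as common to all participants, whereas the variance of a binary outcome changes with the risk. It does not produce the promised relative risk.

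Genmod with a log link does produce relative risks, but the article describes its use as one-level, with no allowance for hospital or for repeated interviews on the same person. For binary outcomes, then, the plan names one procedure that respects clustering and another that gives the stated effect measure, and no procedure that does both.

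An analyst must then either give up the relative risk or give up the clustering. The second choice does most harm where the exposure is a property of the hospital, as process of care is in the article's own example, because the number of hospitals, more than the number of patients, then limits the information.

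**Working it through.** **1. The plan's own figure.** The nearest stated figure is the adult sample size. The inputs from the Adults section are a difference of 5 − 3 = 2 days, SD 4, two-sided alpha 0.05 and a 1:2 split. The larger group needs (1 + 2) × [SD × (z for alpha + z for power) / difference]².

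- 90% power: 3 × [4 × (1.960 + 1.282)/2]² = 126.1, so 127, with 64 in the smaller group. Total 191, as stated.
- 80% power: 3 × [4 × (1.960 + 0.842)/2]² = 94.2, so 95, with 48 in the smaller group. Total 143, as stated.

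Both figures reproduce, and neither depends on this point.

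**2. What each named method can deliver for a binary outcome.**

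| Method named | Allows for clustering as described | Gives a relative risk |
|---|---|---|
| Genmod, one-level | No | Yes (log link) |
| Proc Mixed | Yes | No (risk difference) |
| Cox model | No cluster term stated | No (hazard ratio, time-to-event outcomes only) |

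**3. Illustration of the scale.** One clustered binary data set was simulated with 8 groups, 4,840 records, an assumed baseline risk of 0.30 and a true relative risk of 1.5, so a true risk difference of 0.30 × 0.5 = 0.15. A linear mixed model, the type Proc Mixed fits, returned 0.169, a risk difference. A log-link model with clustering handled by generalised estimating equations (GEE) returned a ratio of 1.56. On the variance, a risk of 0.30 gives 0.30 × 0.70 = 0.210, and a risk of 0.45 gives 0.45 × 0.55 = 0.248. These are not equal, as the linear model assumes.

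**4. Size if one-level Genmod were used instead for a hospital-level factor.** The design effect is 1 + (m − 1) × ICC, where m is the number of people per site. The total of 484 comes from the sample size section. The ICC and the number of sites are assumptions. Population Base names eight or nine hospitals and centres, and adds private specialists' rooms as recruiting sites without a count, so 8 to 25 sites is taken as a range.

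| Sites | m = 484/sites | Design effect, ICC 0.01 | ICC 0.02 | ICC 0.05 | SE understated by a factor of |
|---|---|---|---|---|---|
| 8 | 60.5 | 1.59 | 2.19 | 3.98 | 1.26 to 1.99 |
| 15 | 32.3 | 1.31 | 1.63 | 2.56 | 1.15 to 1.60 |
| 25 | 19.4 | 1.18 | 1.37 | 1.92 | 1.09 to 1.38 |

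The last column is the square root of the design effect at ICC 0.01 and at ICC 0.05. The formula takes sites of equal size.

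A simulation of the same fallback used 8 hospitals of 60 patients, an assumed baseline risk of 0.30, a hospital-level factor with no effect, and 600 runs per setting. The one-level log-link model rejected in 5.5%, 6.2%, 19% and 31% of runs for a between-hospital SD of log risk of 0, 0.1, 0.2 and 0.3, against a nominal 5%.

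**The case against.** The strongest objection is that the article sends hospital-level factors to the mixed model and not to one-level Genmod. A reader might infer that the plan, followed as written, yields intervals that are too narrow and excess false positives. The documents do not support that. As written, such a factor gets a cluster-aware model and the result comes out on a different scale. The figures in step 4 describe only what happens if an analyst falls back on one-level Genmod to obtain the relative risk. This part of the objection stands.

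A reader might also infer that the adult contrast in disability days would be analysed on the wrong scale, or would lose power by being split into a yes/no outcome. Nothing in the article proposes a split, and either named regression procedure gives the difference in mean days directly. The sentence on relative risks refers to the outcomes of interest and does not say that it covers every one.

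Three further limits stand. Adherence is never defined as binary and Table 1 lists no adherence scale, so the missed payment is the firm example. At the one-year primary endpoint there is one record per person, so repeated interviews matter only where several visits are modelled together. Proc Mixed suits the many continuous scales.

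Two replies do not remove the mismatch. Genmod can handle clustering through a REPEATED statement, but the article describes its use as one-level and gives clustering to Proc Mixed. With a single yes/no exposure a ratio can be worked out from the linear fit, (0.2997 + 0.1691)/0.2997 = 1.56 in the illustration. Once covariates are adjusted for, however, the linear model implies no single relative risk.

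Finally, an article may leave software detail to an analysis plan. This one names the procedures, gives each a role and fixes the effect measure, and the three do not fit together for binary outcomes.

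**Conclusion.** The point holds as a mismatch between procedure and effect measure. For binary outcomes in clustered or repeated-interview analyses, the named procedure cannot give the promised estimate. This is firm for the missed household payment, and applies to adherence only if it is analysed as yes/no.

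The statistical harm is conditional. If relative risks for hospital-level factors were taken from one-level Genmod, the variance would be understated by a factor of about 1.6 to 4.0 with 8 sites and 1.2 to 1.9 with 25, for 484 people and an assumed ICC of 0.01 to 0.05. Those factors apply to hospital-level exposures. They should not be carried over to person-level or family-level exposures such as language at home, which vary within hospitals. The adult and total sample sizes are not in question. The correction is worth making before analysis because it is specific and nearly free.

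**What to change.** In the Statistical Analysis section:

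- For binary outcomes in clustered or repeated-interview analyses, replace Proc Mixed with a clustered log-link model. One option is Genmod with a REPEATED statement, a Poisson working variance and robust standard errors corrected for a small number of clusters. The other is Proc Glimmix with random effects for hospital and, where visits are pooled, for patient.
- Keep Proc Mixed for continuous scales.
- Limit relative risks to binary outcomes, and report continuous outcomes, including disability days, as mean differences.
- State whether adherence is analysed as yes/no or as a score, so that it falls under one rule or the other.

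The cost is revised wording and a different procedure call. Data collection and sample size do not change. Intervals for hospital-level factors will be somewhat wider than a one-level model would show.

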### Case ascertainment and consent

The lead clinician at each public or private site will act as the "principal investigator" (PI). The PI will be required to consent potentially eligible cases, or their parent (for potential cases aged 18 years or under), or guardian (for potential cases unable to consent themselves) of people with new diagnoses of epilepsy into the study. Each PI will maintain a log of every potentially eligible patient who is approached to participate in the study. The logs contain the initials and date of birth of the eligible patients, the date they were screened for participation in the study, whether or not consent to participate was obtained and if not, the reason for their non-participation. Participants consent to: 1) the abstraction of information about their epilepsy from medical records; 2) interviews at baseline (as soon as possible after diagnosis), four months and one year (primary endpoint), and; 3) for the participant's general practitioner (GP) to be contacted by research staff if necessary. All PIs or their research staff are contacted weekly to track screening and recruitment.

To ensure identification of all people with a new diagnosis of epilepsy in the SSWAHS who are not seen in a public hospital, regular liaison and collaboration with General Practitioners (GP), paediatricians and private neurologists in the area is essential. Various methods will be used to initiate and maintain a high level of awareness of the study in the community, including 6 monthly contacts to enquire about potentially eligible participants, and provision of pamphlets, magnets, posters and training for clinicians and allied health professionals.

In addition PIs may consent participants with their first unprovoked seizure, who do not currently meet the criteria for a diagnosis of epilepsy, into the SEISMIC First Seizure substudy. These people will be asked to allow 6 monthly contact from the research team to ascertain if there has been any clinical changes that would warrant their subsequent inclusion as a case of new onset epilepsy over the course of the study's recruitment.

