#### 4 month interview

Participants complete a clinical and an age-specific psychosocial assessment covering the four month period since their diagnosis. *The clinical assessment for all participants *consists of a review of seizure frequency since last interview, clinical investigations, medications, general health, developmental milestones and an optional cognitive assessment if deemed necessary by the interviewer. *The adult, parent or carer interviews *are as outlined previously.

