#### 12 month interview

Participants complete a clinical and an age-specific psychosocial assessment covering the previous 8 month period. *The clinical assessment for all participants *is as outlined at the four month assessment with a reassessment of the diagnosis of epilepsy or epilepsy syndrome. *The adult, parent or carer interviews *are as outlined previously.

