#### Specific questionnaires used include

The *EuroQol *(EQ-5D) [46,47] is a measure of quality of life that provides a simple descriptive profile and a single value for health status graded on a scale from -0.59 to 1.00. Lower scores indicate poorer quality of life. A score of 0 represents no quality of life and scores less than 0 represent states perceived by the respondent to be worse than death.

The *Brief Illness Perception Questionnaire *(BIPQ) [48] is a valid and reliable measure of patients' cognitive and emotional representations of their illness across a variety of illness groups. The BIPQ assesses consequences, timeline, personal control, treatment control, identity, coherence, concern, emotional response, and causes of illness. Items are rated using a 0 (not at all) to 10 (severely affects my life) response scale.

Psychosocial disability is assessed using the *12-item World Health Organisation Disability (WHO) Assessment Schedule *(WHO-DAS II) [49]. The 12-item WHO-DAS II assesses the magnitude of disability over the previous 30 days using a five point scale from none to extreme/cannot do. Total scores range from 0-100 with higher scores indicating greater disability.

The *Strengths and Difficulties Questionnaire *(SDQ) [50] is a brief behavioural screening questionnaire for parents of 4 to 16 year olds which screens for child psychiatric disorders. In addition to assessing common emotional and behavioural difficulties, it also asks if the parent/carer/proxy thinks that the child has problems in these areas and if there is associated distress and social impairment. The SDQ consists of 5 domains with 5 items per domain with responses ranging from 0 (not true) to 2 (certainly true) with higher scores indicating more problems.

The A*lcohol Use Disorders Identification Test *(AUDIT-C) [51] uses three questions to collect information on 'at-risk' alcohol consumption. Individual question scores range from zero to four. At risk alcohol consumption is indicated by a total score of five or more for males or four or more for females.

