Information on paid and unpaid work is collected using modified versions of questions 34-51 of the *Australian Bureau of Statistics 2006 Census *[52] relating to jobs and work. Participants are asked to indicate whether there has been any change in employment circumstances since their diagnosis. Specific barriers to return to work are determined using the short form of the *Job Content Questionnaire *(JCQ) [53]. This widely used measure assesses job demands, control over work and support received.

*Household economic hardship *is determined by a series of questions about failure to make household payments and whether there was help provided by any organisation or individual to meet these payments. An advantage of this measure is that it is sensitive to the possibility that individuals prioritise certain payments (e.g. default on power bills to pay rent). The basis for these questions is the US Census Survey of Income and Program Participation [54].

The *Family Adaptation, Partnership, Growth, Affection, Resolve *(APGAR) [55] questionnaire is a valid and reliable 5-item instrument for assessing perceptions of adequacy of social support among adults and children. Items are rated using a three point scale from 'hardly ever' to 'almost always'. Total scores range from 0 (perceives inadequate support) to 10 (perceives adequate social support).

The *Inventory of Family Protective Factors *(IFPF) [56] is a 16-item scale which assesses stressful events the family may have experienced and how they were handled. Item scores range from 1 (not at all like my family) to 5 (almost always like my family). Total scores range from 16 to 80 with high scores indicating a perceived high degree of protection provided by the family.

The *Hospital Anxiety and Depression Scale *(HADS) [57] is used to collect information on depression and anxiety. The HADS is a self-report instrument designed for use with medically ill patients. Scores of 8 (possible range 0-21) or more on the depression or anxiety subscales are classified as 'depressed' or 'anxious', respectively. Consent has been obtained to convey scores of 8 or more directly to participants' nominated GP who will be permitted to arrange treatment or formal referral for abnormal mood symptoms according to their clinical judgement.

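### Kaplan-Meier and Cox models do not suit outcomes recorded only as a state at the 4- and 12-month interviews; a grouped-time hazards model would

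*Protocol article*

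**What the plan says.** The Statistical Analysis section of the protocol article states: "Survival analyses will be used to investigate the time trajectory of risk and protective factors for various poor outcomes". It continues: "Kaplan-Meier survival curves will be produced and then the adjusted survival will be examined using Cox proportional hazards models". The outcomes meant are not listed, and nothing is said about how an event time is defined.

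Under Case ascertainment and consent, participants agree to "interviews at baseline (as soon as possible after diagnosis), four months and one year (primary endpoint"), so there are two interviews after baseline.

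The section on specific questionnaires shows what several instruments capture. The WHO-DAS II "assesses the magnitude of disability over the previous 30 days". For the HADS, "Scores of 8 (possible range 0-21) or more on the depression or anxiety subscales are classified as 'depressed' or 'anxious', respectively". The GHQ-12 refers to the last four weeks, and the modified stigma scale is scored at each interview.

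Other items look back over the whole interval. The 4-month clinical assessment includes "a review of seizure frequency since last interview", and the 12-month visit is a "clinical and an age-specific psychosocial assessment covering the previous 8 month period". Table 1 also lists accidents, falls and injuries, and whether the participant is alive at the scheduled assessment. Change in employment is asked about since diagnosis.

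**The concern.** Kaplan-Meier and standard Cox methods assume that each event has a known time. For a scale that describes the respondent's state around the interview, the data show only that the person was not in the poor state at one interview and was in it at the next. The onset is interval-censored, in a window of 4 months (0-4) or 8 months (4-12). If the interview date stands in for the event date, every event falls late and almost all share one of two times.

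Two things are at stake. First, a published curve would show no events for months and then a sharp drop, which reflects the visit schedule and not the course of the illness. The analysis is meant to describe a time trajectory, and two looks cannot show one. Second, with nearly all events tied, the size of a risk factor's hazard ratio depends partly on a software option. The study's primary aim is to identify modifiable factors, so the size of those effects matters.

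**Working it through.** The article gives no event count, hazard ratio or power for the survival analysis, so there is no stated figure to reproduce.

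**Inputs.** From the article: interviews at 4 and 12 months; an expected cohort of 484; about 30% of adults with psychological morbidity, used here as the exposed share; and a relative risk of 1.5, named in the children's sample-size paragraph and used here as an illustrative hazard ratio. Assumed: constant hazards, no dropout, interviews exactly on schedule, an unexposed 12-month risk of 5-50%, and a true hazard ratio of 1.5 or 2.0.

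**1. Kaplan-Meier.** With a constant hazard and 12-month risk p, true event-free survival is S(4) = (1 - p)^(1/3) and S(12) = 1 - p. With events dated at interviews, the curve stays at 1 until month 4 and at S(4) until month 12.

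- p = 30%: S(4) = 0.70^(1/3) = 0.888. Just before 4 months the curve reads 1.000 against 0.888, an overstatement of 11 points. Just before 12 months it reads 0.888 against 0.700, or 19 points.
- p = 20%: S(4) = 0.80^(1/3) = 0.928. The overstatements are 7 and 13 points.

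At exactly 4 and 12 months the curve is right. No tie method enters this step.

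**2. What each Cox tie method estimates.** Take an unexposed 12-month risk of 30% and a true hazard ratio of 2.0. Survival in the exposed is the square of survival in the unexposed.

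- Months 0-4: risk 1 - 0.888 = 0.112 unexposed and 1 - 0.888² = 0.212 exposed. The risk ratio is 1.89 and the odds ratio 2.13.
- Months 4-12, among those still event-free: risk 0.212 unexposed and 0.378 exposed. The risk ratio is 1.79 and the odds ratio 2.27.

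Within one tied time, the Breslow score equation d1 = (d1 + d0)·n1·r/(n1·r + n0) solves to r = (d1/n1)/(d0/n0), which is the interval risk ratio. The discrete-logistic method targets the interval odds ratio. Pooling the two intervals gives 1.83 and 2.20 respectively. The ratio of -log(1 - risk) is 0.2378/0.1189 = 2.0 in the first interval and 0.4756/0.2378 = 2.0 in the second. A complementary log-log model estimates that ratio, so it recovers the hazard ratio.

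**3. Large-sample limits, 30% exposed.**

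| True HR | Unexposed 12-month risk | Breslow | Efron | Discrete-logistic |
|---|---|---|---|---|
| 1.5 | 5% | 1.49 | 1.50 | 1.51 |
| 1.5 | 20% | 1.46 | 1.50 | 1.55 |
| 1.5 | 30% | 1.43 | 1.50 | 1.58 |
| 1.5 | 50% | 1.38 | 1.49 | 1.65 |
| 2.0 | 5% | 1.97 | 2.00 | 2.03 |
| 2.0 | 20% | 1.89 | 2.00 | 2.13 |
| 2.0 | 30% | 1.83 | 1.99 | 2.20 |
| 2.0 | 50% | 1.70 | 1.96 | 2.40 |

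**4. Simulation check (N = 484, 200 replicates per scenario).** At 30% unexposed risk and a true hazard ratio of 1.5, about 162 events fall on the two times. The estimates are Breslow 1.436, Efron 1.501 and complementary log-log 1.505, against 1.505 from the exact times. With a true hazard ratio of 2.0, they are 1.83, 1.99 and 2.00.

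**The case against.** The strongest reply is that the article never says which outcomes go into the survival analysis. A separate paragraph of the same section sends clinical, psychosocial and economic outcomes to multivariable regression with relative risks, so the HADS, WHO-DAS or stigma scores may never reach a Cox model. Several candidates could carry dates: seizures since the last interview, injuries, employment change and death, from recall or medical records. The article does not say whether dates are collected, and a condensed article may leave that to the full protocol. This stands, and it limits the point to outcomes known only as a state at interview.

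A reader might also infer that hazard ratios will be biased toward the null. The documents do not support that. It needs the Breslow method with common events; Efron is nearly unbiased in the range tried, and the discrete-logistic method moves away from the null. The article does not state the tie method. That detail, like the definition of who is at risk at baseline, is commonly left to the analysis plan, so its absence is not itself a finding.

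Finally, real interview dates will scatter around 4 and 12 months, so there will be fewer exact ties than in the calculation. That softens the tie problem but leaves the interval censoring in place. The Kaplan-Meier error between interviews does not depend on tie handling, and none of these replies removes it.

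**Conclusion.** The point holds for outcomes ascertained only as a state at the 4- and 12-month interviews, such as those based on the HADS, WHO-DAS II, GHQ-12 and stigma scale. For these, Kaplan-Meier adds little to two proportions and misleads between them, by about 11 and 19 percentage points at an assumed 30% risk. Cox estimates would differ by tie method. Over the range tried, the largest Breslow shortfall is about 0.12 on a hazard ratio of 1.5 and 0.30 on 2.0, both at 50% risk. With rare events the differences are small.

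These figures rest on the assumed risks, constant hazards, no dropout and punctual interviews. No method can recover an episode that starts and resolves between interviews, so for reversible states any hazard ratio refers to first being observed in the state. The point does not extend to outcomes with recorded dates, and it does not touch the article's other planned regressions. The change is worth making because a better-fitting model is available at little cost, but the effect on hazard ratios is modest.

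**What to change.** Name the outcomes for survival analysis and say which have a recorded event date. Keep Kaplan-Meier and Cox for those; seizures, injuries, employment change and death are possible candidates.

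For interview-state outcomes, replace them with a grouped-time proportional hazards model: a binary outcome per interval (0-4 and 4-12 months), a complementary log-log link, a separate intercept for each interval, and only participants free of the outcome at baseline. Estimates are still read as hazard ratios. Report the proportions affected at 4 and 12 months in place of Kaplan-Meier curves. If interviews stray far from schedule, an interval-censored model using the actual interview dates serves the same purpose.

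The cost is a change of model statement in Proc Genmod, which the article already plans to use, with no new data. The at-risk set is smaller: if about 30% of adults already have psychological morbidity at baseline, as the sample-size section assumes, roughly 70% of adults remain for a mood outcome.
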